**Table 2 Tab2:** **Schedule of study measurements during the screenings phase and the first treatment set**

		**Mexiletine or placebo** ***(period 1)***				**Wash-out and cross- over**	**Mexiletine or placebo** ***(period 2)***				**Interim analysis 1**	
**Actions**	**Screening**	**Week 1, day 1**	**Week 2, day 1**	**Week 3, day 1**	**Week 4, day 7**	**Week 5**	**Week 6, day 1**	**Week 7, day 1**	**Week 8, day 1**	**Week 9, day 7**	**Week 10**	**Week 11**
**Lab test**	X											
**Pregnancy test**	X											
**Consent**	X											
**Medical history**	X											
**ECG**	X				X					X		
**Needle EMG**					X					X		
**IVR**		X	X	X*	X*		X	X	X*	X*		
**INQoL/SF-36**		X			X		X			X		
**Clinical myotonia tests**		X			X		X			X		
**Quantative grip myotonia**		X			X		X			X		
**Mexiletine blood plasma levels**		X			X		X			X		
**Dispense drug/ placebo**		X										
**Collect medication bottles**					X					X		

Study measurements for a possible second, third and fourth treatment set are identical to the measurements in the first treatment set and are not represented in this table.

X* = daily collection of IVR data.

Patients who exhibit convincing evidence of a genuine positive effect will be offered to continue to use mexiletine (see section: statistical analysis – individual interim analyses). After completion of the individual N-of-1 trials, patients will be followed up for three months, to monitor clinical progression, drug compliance, adverse events and quality of life.

### Safety

ECGs taken at the beginning and end of each treatment period will be screened for abnormalities (conduction times: PR, QRS and QTc-time; and the presence of cardiac arrhythmia by an experienced cardiologist). Cardiac arrhythmias will be classified as clinically relevant or irrelevant. Clinically relevant arrhythmia and conduction disorders will be presented to the Data and Safety Monitoring Board (DSMB).

During the study, patients are instructed to directly report serious adverse events, non-serious adverse events (such as gastro-intestinal discomfort or nausea) are reported during trial visits.

### Quality assurance/monitoring

The Clinical Trial Center of the Radboud University Medical Center Nijmegen, Nijmegen (“Clinical Research Center Nijmegen” (CRCN); www.crcn.nl) will be responsible for the data quality management and monitoring of this trial.

### Ethical approval and registration

This study has been reviewed and approved by the medical ethics committee of the region Arnhem-Nijmegen, The Netherlands, (reference CMO nr. NL34801.091.10) and has been registered at clinicaltrials.gov (ClinicalTrials.gov Identifier: NCT02045667). Patients receive verbal and written information about the study and written informed consent will be obtained before randomization.

### Data safety monitoring board

There will be bi-annual controls by the data safety monitoring board, which consist of a clinical pharmacologist, a cardiologist and a biostatistician. This committee will analyze all severe adverse events, drop-outs due to adverse medical events and mortalities.

### Statistical analysis

#### Sample size and power

The IVR measure for stiffness (a 9-points scale) is our primary endpoint. No minimal clinically important difference (MCID) calculation for the IVR was available from the literature. We chose an MCID of 0.75 on the mean IVR-score as clinically relevant difference based on clinical expert opinion and a previously reported within subject standard deviation (SD) of 1.5 (with ½ SD as a distribution-based estimate for the MCID [44]) [30]. The mean IVR score in the published RCT was 4.21 (95% confidence interval 3.40 - 5.20) on placebo [13]).

The data of the combined N-of-1 trials will be analyzed using a hierarchical Bayesian model [45]. Since no formula-based methodology exists for sample size or power calculations for such designs, we have performed a simulation-based sample size calculation.

The simulation-based sample size calculation consisted of the following steps: (1) Drawing a random realization from a prior distribution for the mean treatment effect, based on expert opinion. (2) For each of these realizations, we have simulated data for 30 N-of-1 trials using R software, where the data for each N-of-1 trial consisted of 2 × 10 × 2 observations (for 2 treatment arms, 10 observations per arm per treatment pair, and 2 completed treatment pairs). These simulations were performed using a model structure with a random intercept and a random slope for different individuals and a residual within-person error. (3) Each simulated data set of 30 N-of-1 trials was analyzed as described by Zucker et al. [22]. We have combined each of the simulated data sets with a normally distributed prior distribution with a mean of 1.75 and a standard deviation of 0.89, which was also based on expert opinion. (4) Each of these Bayesian analyses resulted in a marginal posterior distribution for the mean treatment effect β_0_. (5) For each of these posterior distributions we determined the posterior probability of a treatment effect of at least 0.75. We assumed that all participants will be subjected to two treatment pairs. Steps 1 - 5 were re-iterated 1000 times, resulting in 1000 posterior probabilities of a clinically meaningful treatment effect. From these 1000 probabilities we have determined the mean, which corresponds to an estimate of the expected posterior probability of a substantial treatment effect. The mean expected posterior probability of a clinically meaningful treatment effect was 0.82. Thus, under the specified assumptions, with the results of 30 patients with NDM completing the trial, we would be 82% certain that mexiletine produces a clinically meaningful treatment effect in these patients.

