#### Prior elicitation, informative and non-informative priors

The strength of Bayesian analyses is that it provides an algorithm for updating the probability estimate of a particular claim being true (e.g., the claim that mexiletine produces, on average, an improvement of at least 0.75 on the IVR stiffness scale in patients with NDM, when compared to placebo) whenever novel relevant evidence becomes available. The information that was already available before the novel evidence became available is expressed as prior distributions (so called “priors”). For all model parameters a prior will be needed, however, since the mean treatment difference is the parameter of main interest, these priors will receive the most attention. In the main analysis an informative prior based on data on the treatment effect from the previous study (i.e. treatment effect in the RCT by Statland et al. [13]) will be used. In a sensitivity analysis we will use a prior for the treatment effect based on expert opinion, in which case they are elicited from expert physicians: expert neuromuscular neurologists with experience in the pharmacological treatment of NDM patients. These neurologists will be asked to estimate the treatment effect based on patient demographic information, genetic information and video-clips of the baseline myotonia bedside tests. A histogram-based method (Spiegelhalter ([46], p.145) will be used to elicit individual (i.e. from each neurologist) clinical priors, which will subsequently be aggregated to provide one group clinical prior. Another sensitivity-analysis will be performed with a non-informative prior for the group level mean treatment effect instead of the informative priors. For all other model parameters we will use non-informative (or ‘flat’) priors, since it is difficult to elicit parameters such as random effect variations from physicians [46].

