#### Bayesian hierarchical analysis

This study aims to answer the following questions: What is the probability that mexiletine is clinically effective in patients with non-dystrophic myotonia (NDM) on the individual and group level? To combine the results of the multiple N-of-1 trials, a hierarchical (multi-level) Bayesian model will be used, with the IVR measure for stiffness as the dependent variable, and with the patient and the subgroup (chloride versus sodium channel mutation carriers) as the structural grouping factors (or the levels of the model). The patient will be treated as a random effect (both a random intercept and a random slope), while subgroup of patients and mutation type will be treated as fixed effects. The within person residual variance will similarly be assumed to be drawn from a common distribution. In the main analysis, the prior will be based on the RCT results from Statland et al [13]. Sensitivity analyses with a clinical prior and with a non-informative prior will also be performed. From the Bayesian analysis we will obtain posterior distributions for the mean treatment effect at the population level, as well as posterior distributions for the treatment effects at the individual level, that will exhibit borrowed strength from the population estimates through shrinkage to the population mean. For details of the procedure to be used, see Zucker et al. [22].

Also, we will investigate interactions between treatment effect and treatment set, and between treatment effect and treatment order. Secondary endpoints will be analyzed similarly.

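### The 0.82 expected posterior probability was simulated with an expert-opinion analysis prior, so it does not describe the main analysis, which uses a prior from the previous RCT

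*Protocol article*

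**What the plan says.** All references are to the Protocol article.

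**Sample size and power.** The simulation has five steps, two of which involve a prior for the mean effect.
- Step 1 generates the true effect: "Drawing a random realization from a prior distribution for the mean treatment effect, based on expert opinion". No parameters are given.
- Step 3 analyses each simulated data set of 30 patients by combining it with a normal "prior distribution with a mean of 1.75 and a standard deviation of 0.89, which was also based on expert opinion".
- Step 5 takes the posterior probability of an effect of at least 0.75. The mean over 1000 runs is 0.82, which the text reads as 82% certainty of a clinically meaningful effect, under the specified assumptions.

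**Prior elicitation, informative and non-informative priors.** "In the main analysis an informative prior based on data on the treatment effect from the previous study" is to be used, namely the cross-over RCT. Expert opinion has another role: "In a sensitivity analysis we will use a prior for the treatment effect based on expert opinion". That prior is still to be elicited from neurologists by a histogram method.

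**Bayesian hierarchical analysis.** The same allocation is repeated: "In the main analysis, the prior will be based on the RCT results", and "Sensitivity analyses with a clinical prior and with a non-informative prior will also be performed". The Methods/Design part of the Abstract also names the RCT as the informative prior.

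**The concern.** The priors in steps 1 and 3 have different jobs. The step-1 prior describes plausible true effects and may properly differ from the analysis prior. Step 3 stands in for the analysis that will be run, and the probability in step 5 inherits its prior. If 0.82 is to say what the main analysis can be expected to deliver, step 3 needs the main-analysis prior. It has another one, and the article does not say why.

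What is at stake is how the stated certainty is read. A prior built from RCT data may be much tighter than SD 0.89 and so supply a large part of the final posterior. The article then shows neither the expected certainty of the main analysis nor how much of it would come from the RCT and how much from the 30 new patients. That separation matters here because the second study objective is to compare this approach with a conventional RCT.

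**Working it through.** **Inputs from the article (Sample size and power):** threshold 0.75; within-subject SD 1.5; 30 patients; 2 pairs with 10 observations per arm per pair, so 20 per arm; step-3 prior N(1.75, 0.89).

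**Not in the article, so assumed:** step-1 prior N(1.75, 0.89); random-slope SD τ from 0.5 to 1.5; RCT-based prior with mean m from 0.75 to 2.5 and SD s from 0.2 to 0.45. For the RCT, the article gives only the placebo mean, 4.21 (3.40 to 5.20).

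**Method:** a normal approximation for the population mean effect.
- Standard error of the estimated mean effect: se = √[(τ² + 2·1.5²/20)/30] = √[(τ² + 0.225)/30]. This gives 0.126, 0.202 and 0.287 for τ = 0.5, 1.0 and 1.5.
- Share of posterior precision from the prior: p = se²/(s² + se²).
- Expected posterior probability: Φ{[(1−p)·1.75 + p·m − 0.75] / √[s²se²/(s²+se²) + (1−p)²(0.89² + se²)]}.

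**The stated figure first.** With N(1.75, 0.89) in both steps, the expected posterior probability equals the prior probability: Φ[(1.75 − 0.75)/0.89] = Φ(1.124) = 0.869, whatever τ is. The stated 0.82 is not reproduced on this assumption. The Monte Carlo error with 1000 runs is about 0.01. However, a step-1 prior of N(1.565, 0.89) or N(1.75, 1.09), with step 3 unchanged, gives 0.82 to 0.83. The gap therefore depends on an input that is not stated, and the present point does not rest on it.

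**Changing only the step-3 prior:**

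| Step-3 prior | τ = 0.5 | τ = 1.0 | τ = 1.5 | Prior's share of precision |
|---|---|---|---|---|
| Expert N(1.75, 0.89) | 0.869 | 0.869 | 0.869 | 2%, 5%, 9% |
| Flat | 0.865 | 0.858 | 0.847 | 0 |
| RCT N(0.75, 0.2) | 0.864 | 0.852 | 0.827 | 28%, 51%, 67% |
| RCT N(1.0, 0.3) | 0.875 | 0.881 | 0.887 | 15%, 31%, 48% |
| RCT N(1.75, 0.45) | 0.882 | 0.900 | 0.921 | 7%, 17%, 29% |
| RCT N(1.75, 0.3) | 0.902 | 0.938 | 0.970 | 15%, 31%, 48% |
| RCT N(1.75, 0.2) | 0.937 | 0.983 | 0.998 | 28%, 51%, 67% |
| RCT N(2.5, 0.2) | 0.968 | 0.998 | 1.000 | 28%, 51%, 67% |

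Worked cell, lowest value (m = 0.75, s = 0.2, τ = 1.5):
- se² = (2.25 + 0.225)/30 = 0.0825, and p = 0.0825/0.1225 = 0.673.
- Numerator: 0.327·1.75 + 0.673·0.75 − 0.75 = 0.327.
- Denominator: √(0.0269 + 0.1066·0.8746) = 0.347.
- Φ(0.942) = 0.827.

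Over the assumed range the main-analysis figure runs from about 0.83 to 1.00, and the RCT prior's share of precision from about 7% to 67%. Widening τ to 2 lowers the bottom end to about 0.79.

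**The case against.** The best defence is that the simulation used a deliberately vague prior. At SD 0.89 the expert prior carries 2% to 9% of the posterior precision, and the result (0.869) is close to the flat-prior result (0.847 to 0.865). On these assumptions the simulated analysis rests almost wholly on the 30 new patients, which is arguably a stricter basis for sizing than one that borrows from the RCT. Most of the RCT-type priors tried give a figure as high or higher. The article also names the prior it used and makes its claim conditional on the stated assumptions.

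Much of this stands. Sizing on a vaguer prior can be defended, but the article does not present 0.82 in that way. It gives the figure as the certainty to be expected from the trial and offers none for the main analysis.

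Four stronger readings are tempting but not supported:
- **That 0.82 describes the planned expert-prior sensitivity analysis.** That prior has yet to be elicited, and nothing says it will be N(1.75, 0.89).
- **That the main analysis is defined with two rival priors.** The Abstract and the two analysis sections agree on the RCT prior; the sizing section reports a completed simulation.
- **That 0.82 is a miscalculation.** The step-1 parameters and slope SD are not given, and plausible step-1 priors return about 0.82.
- **That 30 patients are too few.** Nothing here shows it.

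**Conclusion.** The point holds as a mismatch between the sizing and the main analysis. The prior in step 3 is not the one chosen for the main analysis, so the 0.82 and the 82% certainty drawn from it are not properties of that analysis, and no other group-level operating characteristic is stated. The mismatch itself is read directly from the text and needs no assumption.

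Its size does need assumptions. The range of about 0.83 to 1.00 depends on an assumed RCT mean and SD, an assumed slope SD, true effects drawn from N(1.75, 0.89) and a normal approximation. The direction is not guaranteed: a favourable RCT prior raises the figure, while a tight one centred at 0.75 lowers it below the expert-prior value of 0.869. The firmer consequence is interpretive. The main analysis may take far more of its posterior from the prior than the simulated one did, and the article does not let the reader see how much.

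**What to change.** Rerun step 3 with the RCT-based prior specified for the main analysis. Keep the expert prior as the step-1 source of true effects and state its parameters. Report the result as the main-analysis figure in place of 0.82. Beside it, give the figures under the expert prior and under a non-informative prior, each labelled as such, so that the contribution of the 30 new patients is visible. Stating the RCT prior's mean and SD and the variance components used would make all three figures checkable.

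The cost is one rerun of existing code and a restated figure, with no extra patients, visits or data. The drawback is that the new headline figure may depend more on the prior than the present one, which is why the other two should stand next to it.

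### The mean posterior probability of 0.82 does not justify 30 patients and does not follow from the stated inputs: the stated prior alone gives 0.87 with no patients

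*Protocol article*

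**What the plan says.** The protocol article, under Study population, bases the thirty patients on a sample size calculation, which is set out under Sample size and power. Step 1 is described as "Drawing a random realization from a prior distribution for the mean treatment effect, based on expert opinion"; no mean or SD is given for it. Step 2 simulates 30 N-of-1 trials per draw ("for 2 treatment arms, 10 observations per arm per treatment pair, and 2 completed treatment pairs"). Step 3 combines each data set with "a normally distributed prior distribution with a mean of 1.75 and a standard deviation of 0.89, which was also based on expert opinion". Steps 4 and 5 take the posterior probability that the mean effect is at least 0.75. After 1000 repetitions these probabilities are averaged: "The mean expected posterior probability of a clinically meaningful treatment effect was 0.82". The article concludes that, under its assumptions, "with the results of 30 patients with NDM completing the trial, we would be 82% certain that mexiletine produces a clinically meaningful treatment effect". No other sample size and no target value are reported.

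The next section, on priors, sets the prior of the main analysis: "In the main analysis an informative prior based on data on the treatment effect from the previous study". Expert opinion is used there for a sensitivity analysis.

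**The concern.** When true effects are drawn from a prior and the data are analysed with that same prior under the same model, the average posterior probability of any claim equals its prior probability, whatever the amount of data. An average of this kind can therefore look reassuring without saying anything about the information in 30 patients. Here it is also lower than the value the stated prior gives with no data.

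At stake is the stated basis for the sample size. The article does not give the probability that the trial ends with a convincing answer, nor the probability that it seems convincing when the true effect sits just at the clinically relevant difference. A reader who takes the certainty sentence at face value will expect a final posterior probability near 0.82, which is an unlikely result.

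**Working it through.** **Inputs from the article (Sample size and power):** threshold 0.75; analysis prior N(1.75, SD 0.89); 30 patients; 20 observations per arm per patient (10 × 2 sets); 1000 repetitions.

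**Assumptions:** residual SD 1.5 (the article gives this within-subject SD when deriving the clinically relevant difference, and its use in the simulation is assumed); SD of patient-level treatment effects τ = 0.5 to 2 (not given). The variance of the estimated mean effect is then V = (τ² + 2 × 1.5²/20)/N = (τ² + 0.225)/N.

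**1. Prior alone, no patients.** Φ((1.75 − 0.75)/0.89) = Φ(1.124) = 0.869. Rounding of the mean and SD allows 0.867 to 0.872.

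**2. Attempt to reproduce 0.82 with the stated prior in steps 1 and 3.** In the normal model the mean posterior probability is 0.869 at N = 0, 2, 5, 10, 30, 100 and 1000, for τ = 0.5, 1 and 2. Estimating the variance with a flat prior on the SD (4000 simulated trials per setting) gives 0.868 to 0.874 at N = 30. The Monte Carlo standard error for 1000 repetitions is at most √(0.869 × 0.131/1000) = 0.0107, so 0.82 is at least (0.869 − 0.82)/0.0107 = 4.6 standard errors low. Chance does not explain the gap.

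**3. A different drawing prior N(m, s) in step 1.** With w = (1/V)/(1/V + 1/0.89²) and posterior variance v = 1/(1/V + 1/0.89²), the mean posterior probability is

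Φ( [(1 − w) × 1.75 + w × m − 0.75] / √(v + w²(s² + V)) ).

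It starts at 0.869 with no data and tends to Φ((m − 0.75)/s), the drawing prior's own probability. Solving for 0.82 at N = 30 over τ = 0.5 to 2:

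| Drawing prior | N = 0 | N = 10 | N = 30 | N = 1000 |
|---|---|---|---|---|
| SD 0.89, mean 1.53–1.56 | 0.869 | 0.822–0.832 | 0.820 | 0.810–0.819 |
| mean 1.75, SD 1.10–1.16 | 0.869 | 0.823–0.838 | 0.820 | 0.806–0.818 |

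So 0.82 can arise, but in these cases the figure is highest with no patients and moves only 0.2 to 1.8 points between N = 10 and N = 30.

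**4. What individual trials would show.** With matched priors at N = 30 and τ = 0.5 to 2, 69–81% of simulated trials end with a posterior probability above 0.95, 6–10% end below 0.20, and only about 3–9% end between 0.70 and 0.90.

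**5. A measure that can be interpreted.** Take the chance that the posterior probability reaches 80%, the bar the article uses for individual patients under Individual interim analyses. With a flat prior and true effect δ it is Φ((δ − 0.75)/√V − 0.842).

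- δ = 0.75: Φ(−0.842) = 0.20 at any N. With the expert prior it is about 0.24–0.33 at N = 30.
- δ = 1.75, flat prior, τ = 1: at N = 10, V = 0.1225 and Φ(1/0.350 − 0.842) = Φ(2.02) = 0.98; at N = 30, V = 0.0408 and the result is about 1.00.
- δ = 1.75, flat prior, τ = 2: at N = 10, V = 0.4225 and Φ(1/0.650 − 0.842) = Φ(0.70) = 0.76; at N = 30, V = 0.1408 and Φ(1/0.375 − 0.842) = Φ(1.82) = 0.97.

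**The case against.** The strongest reply is that the article never says steps 1 and 3 share a prior. It says only that the second was also based on expert opinion. Using different priors for design and analysis is legitimate, and a drawing prior a little less optimistic than the analysis prior yields 0.82. The drawing prior, the slope SD and the simulation's residual SD may well be in the full protocol. This stands. A reader might infer that the figure never depends on the number of patients, or that 0.82 is an arithmetic error. The documents support neither: exact invariance needs matched priors and models, and 0.82 is unreproduced, not disproved. A reader might also infer that the plan says the trial lowers certainty from 87% to 82%. The article never states 87%, and its conclusion is conditional on its assumptions.

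The reply does not rescue the sample size, because with the stated analysis prior a value of 0.82 mainly restates an unreported prior. A flat analysis prior would make the average rise with N (0.833 to 0.865 at N = 30), but that contradicts the informative prior stated in step 3.

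A second fair point concerns the replacement measure. Under the expert prior, the chance of reaching 80% is 1.00 with no patients, because 0.869 already exceeds the bar, and with τ = 1 it moves only from 0.81 to 0.83 between N = 10 and N = 30 when averaged over that prior. It is informative only with the non-informative prior and at fixed true effects.

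Third, simulating with the expert prior does not contradict a main analysis based on the RCT. It means only that the planned main analysis was not the one simulated. That is a secondary point.

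**Conclusion.** The concern holds in conditional form. The stated prior gives 0.87 with no patients. With that prior in both steps, 0.82 cannot arise beyond chance (about 5 Monte Carlo standard errors). With a different, unreported drawing prior it can, but it then says little about 30 patients. On either reading the average does not justify N = 30, and the certainty sentence misdescribes a pre-data average as the expected result.

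The value 0.869 and its constancy in N under matched priors rest on the stated prior and on an analysis model that matches the simulation model. The decline in N was shown only for the drawing priors tried. The spread of individual results and the figures in step 5 rest on the assumed residual SD of 1.5 and τ of 0.5 to 2. Nothing here shows that 30 patients are too few: at a true effect of 1.75 the chance of reaching an 80% posterior is about 0.97 to 1.00 with a flat prior. This is a correction to the stated justification, worth making but not a reason to hold the trial.

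**What to change.** Under Sample size and power:

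- State the mean and SD of the step 1 prior, and explain why the result is 0.82 when the stated prior alone gives 0.87; correct the figure if it was an error.
- Delete the sentence that converts the average into 82% certainty.
- From the same simulation, report the probability that the posterior probability of an effect above 0.75 reaches a pre-stated bar, for example 80%. Give it at fixed true effects of 0.75 and 1.75 and averaged over the stated drawing prior, for several sample sizes. Do this with the non-informative prior and with the RCT-based main-analysis prior, and name the prior beside each figure. The expected width of the posterior interval at several sample sizes is an acceptable alternative.
- State the slope SD and residual SD used.

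The cost is a rerun or re-summary of an existing simulation and a few replaced sentences. No patients are added, and N = 30 and the planned analyses can stay as they are.
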